## Abstract

**Background:**

The epidemic of Alzheimer's disease (AD) represents a significant challenge for the health care and social service systems of many developed countries. AD affects both patients and family caregivers, on whom the main burden of care falls, putting them at higher risk of stress, anxiety, mortality and lower quality of life. Evidence remains controversial concerning the effectiveness of providing support to caregivers of AD patients, through case management, counseling, training, technological devices and the integration of existing care services. The main objectives of the UP-TECH project are: 1) to reduce the care burden of family caregivers of AD patients; and 2) to maintain AD patients at home.

**Methods/design:**

A total of 450 dyads comprising AD patients and their caregivers in five health districts of the Marche region, Italy, will be randomized into three study arms. Participants in the first study arm will receive comprehensive care and support from a case manager (an *ad hoc* trained social worker) (UP group). Subjects in the second study arm will be similarly supported by a case manager, but in addition will receive a technological toolkit (UP-TECH group). Participants in the control arm will only receive brochures regarding available services. All subjects will be visited at home by a trained nurse who will assess them using a standardized questionnaire at enrollment (M0), 6 months (M6) and 12 months (M12). Follow-up telephone interviews are scheduled at 24 months (M24). The primary outcomes are: 1) caregiver burden, measured using the Caregiver Burden Inventory (CBI); and 2) the actual number of days spent at home during the study period, defined as the number of days free from institutionalizations, hospitalizations and stays in an observation unit of an emergency room.

**Discussion:**

The UP-TECH project protocol integrates previous evidence on the effectiveness of strategies in dementia care, that is, the use of case management, new technologies, nurse home visits and efforts toward the integration of existing services in an ambitious holistic design. The analysis of different interventions is expected to provide sound evidence of the effectiveness and cost of programs supporting AD patients in the community.

**Trial registration:**

ClinicalTrials.gov: http://NCT01700556

## Background

The *World Alzheimer Report* estimated that there were 35.6 million people living with dementia worldwide in 2010, and according to forecasts this figure will reach 65.7 million by 2030 and 115.4 million by 2050 [1]. The Italian National Institute of Statistics (Istat) estimated that there were approximately 250,000 people suffering from Alzheimer’s disease (AD) and similar dementias in Italy in 2005 [2]. However, since AD and various forms of age-related cognitive deterioration have complex diagnoses, their prevalence is likely to be underestimated [3,4].

AD causes progressive cognitive and functional decline [5], it can have a significant impact on care costs, and is the major cause of nursing home admission [6]. To accurately estimate the societal impact of AD, one needs to consider that patients' families are also affected, since the burden of care in many countries, including Italy, mainly falls on them. AD is known as a ‘family illness’, because family caregivers of AD patients often represent hidden secondary patients [7]. They frequently experience high levels of stress, associated with a higher risk of developing mood disorders, depression, insomnia and a lower quality of life [8]. Anxiety and stress also increase their likelihood of developing physical problems, such as headache, back pain and excess weight, and exposes them to a higher rate of mortality compared to their non-caregiver counterparts [9,10].

Despite controversies [11], promising intervention studies have shown that specific interventions aimed at supporting caregivers of AD patients can lead to significant improvements in their physical and mental health, by reducing caregiver burden and stress [12]. For instance, caregivers receiving specific counseling sessions provided care for longer and delayed the institutionalization of their relatives with AD [13-17]. Counseling of family members delayed admission of the patient to a long-stay facility for an average of 18 months [13]. An experimental program of intensive training, followed by 10 days of follow-up contacts, delayed the institutionalization and reduced the level of caregiver stress [13,18]. In the USA, telephone-based psychosocial support was effective at lowering caregiver stress [19], suggesting that such interventions can provide an interesting low-cost solution to support caregivers.

In this context, new technologies applied to the home hold great potential to improve the quality of life of AD patients and their caregivers. Despite the absence of definitive evidence [20], pilot studies revealed that home adaptations designed to assist older people in fulfilling their daily needs in the home are particularly important for users' quality of life and well-being [21]. Several studies assessing the effectiveness of assistive technology in AD have been undertaken; however, most of these interventions are in a prototype/testing phase and fail to be scaled-up and systematically implemented in daily practice. A few of these include: talking lights, the Home Assurance System project [22], the ROSETTA project [23] and the ENABLE project [24]. The latter project involved the testing of an integrated system of technologies in the home, including automatic night lights, locators for lost objects, computerized calendars, programmable telephones, gas sensors, touch screen pads for music and a voice prompter when medicines should be taken.

One of the largest intervention studies undertaken in the field is the Resources for Enhancing Alzheimer's Caregiver Health (REACH) project, which was launched in the USA in 1995 [25]. Sponsored by the National Institute on Aging and the National Institute of Nursing Research, the main objective was to develop a psychosocial intervention to improve the living conditions of caregivers of AD patients. The REACH project implemented a multi-component intervention, including: 1) individual support of caregivers; 2) group support and family therapy; 3) training of caregivers; 4) interventions to adapt to the home; and 5) the use of technology support systems (for example a telephone-linked computer system and a computer telephone integration system). Evidence suggests that the program was effective at both improving caregivers' quality of life and in delaying the institutionalization of AD patients [8,26], and even today this multi-site intervention represents a major testbed for evidence-based evaluation of practices in the field of dementia care.

An important issue to consider when implementing programs to improve care pathways for AD patients is that the care of these patients is an extremely complex process. Public welfare professionals must take into account multiple care needs (for example health, social and legal), without neglecting the importance of the caregiver and their needs as well. The multidimensionality of this problem not only calls for new services, but also for a greater coordination and integration of existing community health care and social services, within the public, non-profit and private sectors. This was the assumption underlying several projects integrating health care and social services, thus reducing cost, and eliminating waste and inefficiency [27-30]; however, none of these specifically addressed AD patients and their caregivers. Among the tools used in these studies to foster integration of care are case management strategies, staff training and the use of new information technology (IT) systems.

The Italian welfare system has traditionally relied on a family-based approach to older people care. Here, the level of formal care provision has always been marginal when compared to other Western welfare systems, such as those of the UK, Germany and Scandinavian countries [31]. However, stimulated by the increasing dimension of AD and its consequences on families, the Italian Ministry of Social Welfare decided to invest in the innovation of care services in this field. A call for proposals was issued in 2010 addressing public service providers, with the aim of developing innovative interventions, and improving the effectiveness of care for AD patients and their caregivers in the Italian regions.

Responding to this call and building on the knowledge retrieved in the literature, the Italian National Research Centre on Aging (INRCA) in partnership with the Government of the Marche region, developed the proposal of the UP-TECH intervention study, which was successfully evaluated and funded with a grant of approximately 1 million euros. The ambitious idea underlying this project is to create a multi-component intervention program at regional level, which could engage professionals working in both the social and health care services, in a large-scale organizational change to restructure the processes of AD care. For these reasons, a study has been designed following the trial methodology and adapting to the Marche region the most promising evidence-based interventions in this area.

The main project objectives of the UP-TECH study are: 1) to reduce the care burden of family caregivers of AD patients; and 2) to maintain AD patients at home.

Secondary objectives of the project are: 1) to ensure continuity of care and the integration of care pathways; 2) to create an information management system specific for AD; and 3) to evaluate the cost-effectiveness of a case management program for AD patients and their caregivers.

## Methods/design

### Study design

UP-TECH is a multi-component, randomized, controlled trial, lasting 12 months, and enrolling dyads composed of an AD patient and their primary family caregiver. A total of 450 dyads, living in five different health districts of the Italian Marche region, will be randomized into three arms: 1) 150 dyads provided with systematic and comprehensive support of a trained social worker acting as case manager and receiving three nurse home visits (UP group); 2) 150 dyads provided with systematic and comprehensive support of a trained social worker acting as case manager, receiving an assistive technology intervention and three nurse home visits (UP-TECH group); and 3) 150 dyads receiving ‘light’ support in the form of a paper brochure and three nurse home visits (control group).

#### Eligibility criteria

AD patients are subjects with a pre-existing diagnosis of AD, in an intermediate stage, according to the 2011 criteria of the National Institute on Aging-Alzheimer's Association (NIA-AA) [32-34], with a mini-mental state examination (MMSE) score [35] between 10 and 20, living in the community, and assisted by at least one family caregiver.

Family caregivers are defined as those kin either living or not living with the patient (if not habitually living with the patient, then living in the same municipality), who care for and directly support the patient with the activities of daily living (ADL) and instrumental activities of daily living (IADL) for at least 1 hour per day within the last 6 months. Where there is more than one family caregiver, the primary caregiver, that is, the family member who spends more hours assisting the patient, will be included in the trial.

The exclusion criteria are: 1) lack of informed consent from the AD patient or caregiver. If the patient has been declared legally incompetent or has a support administrator appointed, informed consent will be requested from a family member or from a person appointed by a judge. In the case of natural incapacitation, verified by Alzheimer Evaluation Unit (AEU) doctors, consent for the patient will be requested from the primary caregiver; 2) presence of severe diseases associated with disability in ADLs, life expectancy less than 6 months in addition to AD, or unstable chronic conditions in both the AD patient and the family caregiver, as assessed by the AEU and other professionals in the health district; 3) intention of moving out of the health district within 12 months; 4) enrolled in another experimental trial; and 5) lack of a family caregiver or a caregiver less than 18 years old.

#### Outcomes of the study

The main outcomes of the study are: 1) caregiver burden, measured using the Caregiver Burden Inventory (CBI) multi-dimensional questionnaire, administered by a trained nurse. The CBI has five subscales: time-dependence burden, developmental burden, physical burden, social burden and emotional burden, and includes a set of 24 items evaluated using a 5-point Likert scale ranging from 0 (not at all) to 4 (very much), which are summed. A total score higher than 36 indicates a risk of stress, whereas scores near or slightly above 24 indicate a need to seek some form of respite care [36]. During the study, the Italian version of the CBI validated by Marvardi and colleagues will be used [37]; and 2) the actual number of days spent at home by the AD patient during the observation period, defined as days free from episodes of institutionalizations, inpatient hospitalizations and brief stays in an observation unit of an emergency room. This outcome will be treated as a continuous variable and will be calculated at each assessment (6 months, M6; 12 months, M12; and 24 months, M24) by subtracting from the total days of observation, the number of days of institutionalization in an assisted residence facility, care home and/or nursing home inpatient, hospitalizations, and brief stays in an observation unit of an emergency room.

In addition, the following outcomes will be evaluated at the end of the trial: 1) quality of life of the caregiver of the AD patient, measured using the Italian validated version of the quality of life questionnaire, SF-12 [38,39]; 2) anxiety and depression of caregivers, measured using the Italian validated version of the Hospital Anxiety and Depression Scale (HADS) [40,41]. HADS is a 14-item scale, seven of the items relate to anxiety and seven relate to depression, each item is a Likert scale scoring from 0 to 3, and this means that the overall score for either anxiety or depression will be between 0 and 21; and 3) abuse and mistreatment risk of AD patients, using the CASE instrument, an 8-item screening tool designed to assess caregivers for potential abuse. Answers are either given as ‘yes’ or ‘no’, and an answer of ‘yes’ for a question equals one point. A score of four or more is considered ‘abuse likely’, but a score of one can also mean that abuse is likely, depending on the question [42]. An Italian validation of this instrument is planned in a separate study at the end of the trial.

#### Sample size calculation

An estimation of the sample size was carried out by considering the two main outcomes separately.

The first principal outcome is caregiver burden. A previous Italian study estimated that the level of burden of AD patients' caregivers, as measured by the CBI [36], was equal to 32.5, with a standard deviation (SD) equal to 18 [37]. The planned sample size of 150 caregivers is sufficient to detect an effect that lowers the CBI score to 24, with a SD equal to 12 in the treatment group and a null effect in the control group. The statistical power was fixed at 80%, with a 0.05 significance level and a drop-out rate equal to 15%. A CBI score of 24 coincides with a ‘sentinel’ level beyond which it is suggested that caregivers need to receive additional support from the health care and social services.

The second principal outcome is actual days spent at home by the AD patient in the past year. The hypothesis that this outcome is the same in the treated and the untreated populations will be tested. The calculation was made considering a type 1 error (α error) of 0.05, using a one-tailed t-test and assuming a 10% difference between values. Regarding this as the smallest effect of clinical relevance, a sample of 150 patients per treatment group, with a drop-out rate equal to 15%, will be adequate to achieve an 80% probability of rejecting the null hypothesis.

#### Recruitment and screening

In the absence of a regional AD registry, lists of AD patients will be requested from AEUs of the five health districts (Pesaro, Ancona, Macerata, Fermo and San Benedetto del Tronto). The AEUs were established in Italy in 2000 with the aim of improving the care pathways for AD patients. AEUs are multidisciplinary teams, usually led by a neurologist or a geriatrician, with a double-fold task: 1) performing a diagnosis of AD according to the most recent clinical recommendations; and 2) prescribing cholinesterase inhibitors, memantine and atypical antipsychotics under the reimbursement scheme of the Italian health care system. Thus, the patients followed by the AEUs are those using the aforementioned drugs and receiving regular follow-ups by the physicians working in the units. These patients do not usually receive other care services, except from AEUs as consequences of AD. The AEUs will provide the lists of AD patients matching the inclusion criteria. Only prevalent patients will be extracted and eligible to participate in the study. Since local AD evaluation units do not share IT systems, a general list of patients will be created in order to randomly select subjects to be enrolled in the study. Inclusion and exclusion criteria will then be applied to those patients.

#### Randomization, allocation and blinding

A letter with an invitation to participate in the project will be sent to a list of potential participants, randomly extracted from the AEU registers. A total of 640 invitations will be sent, considering a response rate of 70% (a reasonably high rate, since the project has been endorsed by the Italian regional health system and several local patients' organizations). Families agreeing to be contacted will receive a home visit by a nurse. Both caregivers and patients will be requested to sign a full informed consent to participate in the study. The nurses who will make the home visits and administer the questionnaires will be blinded at their first visit.

The allocation sequence will be generated using the statistical software STATA (College Station, TX, USA). Dyads in blocks of 15 and consequently enrolled will be sent by a nurse coordinator in the five health districts directly to the project manager (CC). In each block, five dyads will be allocated to each arm. The randomization will be performed by the project manager, who will not conduct any assessment related to treatment outcomes or have any contact with line staff involved in the intervention, in order to preserve allocation concealment and prevent selection bias (Figure 1).

**Figure 1 F1:**
[figure not shown]
The recruitment process in the UP-TECH project.

#### Interventions

### Case manager intervention

An *ad hoc* trained and hired case manager social worker will systematically and comprehensively support each patient-caregiver dyad in the UP and UP-TECH groups. The underlying concept of case management is inspired by the guidelines of the Case Management Society of America [43]. According to this definition, case management can be defined as ‘a collaborative process of assessment, planning, facilitation, care coordination, evaluation, and advocacy for options and services to meet an individual’s and family’s comprehensive health needs through communication and available resources to promote quality cost-effective outcomes’.

Before starting the trial, all case managers will attend an 8-day intensive and multidisciplinary course, which will address the following subjects: 1) clinical, psychological and social consequences of AD; 2) organization of health and social care services for AD patients; 3) fiscal and law benefits for AD patients; 4) counseling for caregivers; 5) methodology of multidisciplinary work; 6) bioethics; and 7) use of new technology for care. After the course, each case manager will meet on a monthly basis with a senior social worker, who will act as supervisor of the group in order to share experiences and receive advice on the most difficult cases.

The following support will be provided by a case manager: 1) at least three sessions of individual face-to-face counseling, focusing on topics such as housing arrangements, disease awareness and problem solving (following an initial meeting, two reinforcing sessions will be held at 4 and 8 months); 2) monthly follow-up telephone calls; 3) stress management training; 4) information about services/aid/certification/subsidies offered by the Italian national health service, municipal social services and local volunteer organizations (for example information on health care services, support connecting to general practitioners, health service units (medical specialists, hospital services) and social services); and 5) coordination of professionals working in different care settings, and between hospital and community doctors in the case of hospital discharge.

All these services will be addressed with both parties of the dyad and can be intensified when either the caregiver or the patient shows signs of anxiety, stress or poor health, which could also emerge during interviews. Each case manager will handle up to 30 dyads, out of a total of 300 dyads (150 in the UP group and 150 in the UP-TECH group). The placement of the case manager within the network of existing health care and social services in the community will be made following a thorough analysis of care processes in order to facilitate their integration.

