#### Statistics

The first step of the analysis will be exploratory in nature. A descriptive analysis of the sample will be conducted using uni- and bi-variate statistical analyses, with the aim of verifying the comparability of the three study groups. Significant differences between exposures and outcomes will be compared using the chi-square test, Fisher’s exact test (in the case of categorical variables), t-test or analysis of variance (ANOVA) test (for comparisons of continuous variables between groups according to a normal or non-normal distribution). Additionally, to check possible selection bias, the characteristics of the subjects in the sample will be compared to those of non-respondents for available variables (for example age, gender, place of living and MMSE score).

The primary outcome, caregiver burden inventory, will be compared between the three groups using analysis of covariance (ANCOVA). The analyses will adjust for variables which are non-homogenously distributed in the three groups and control for other factors that the literature suggests are associated with the two outcomes (for example gender and age of caregivers, severity of dementia, and use of private care workers) [46,47].

The primary outcome, number of days spent at home by the AD patient during the observation period, will be similarly analyzed using ANCOVA. The events of hospitalizations and institutionalization will also be analyzed with the following: the distribution of events and event-free survival (days spent at home) will be described for the entire sample using Kaplan-Meier estimator modeling; Mantel-Cox log-rank test or generalized Gehan-Breslow-Wilcoxon test will be used to evaluate bivariate differences in survival distribution between identified subgroups; Cox proportional hazard modeling will be used to analyze the multivariate effects of identified risk factors and other determinants on time spent at home under the proportional hazards assumption; and adjusted hazards ratio (HR) and 95% confidence intervals (CI) will be calculated to test the direction and strength of the influence of individual factors on event-risk and event-free survival. The analyses of outcomes will be intention-to-treat (ITT).

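### Case managers cluster the dyads in the two active arms only, but the planned ANCOVA and the sample size treat all dyads as independent

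*Protocol article*

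**What the plan says.** The Case manager intervention section says that a trained social worker "will systematically and comprehensively support each patient-caregiver dyad in the UP and UP-TECH groups". On workload it adds: "Each case manager will handle up to 30 dyads, out of a total of 300 dyads". It does not give the number of managers or say how they are assigned to dyads.

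Control dyads have no case manager. The Study design section describes their care as light "support in the form of a paper brochure and three nurse home visits (control group".

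Randomisation is by dyad, in blocks of 15: "In each block, five dyads will be allocated to each arm" (Randomization, allocation and blinding).

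In the Statistics section the CBI "will be compared between the three groups using analysis of covariance (ANCOVA"), and days at home "will be similarly analyzed using ANCOVA". Adjustment is for unbalanced variables and for known correlates, "for example gender and age of caregivers, severity of dementia, and use of private care workers". All the named examples are characteristics of the dyad. No manager term, random effect or cluster-robust variance is mentioned. The Sample size calculation section treats the groups as independent samples, with no ICC or design effect.

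**The concern.** The intervention is largely the case manager's own work: counselling, stress-management training, monthly calls and coordination of services. Managers will differ in skill and in their reach into local services. Dyads served by the same manager may therefore have correlated burden scores and correlated days at home. That correlation arises in UP and UP-TECH but has no counterpart in control, so the design is partially nested.

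An ANCOVA with independent errors counts each treated dyad as a full unit of information. With a positive ICC, the mean of an active arm is less precise than the model reports. Confidence intervals against control are then too narrow, and false-positive findings more frequent than stated, on both primary outcomes. Randomising dyads individually does not remove this, because the clustering arises after allocation, through delivery.

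**Working it through.** **Inputs from the protocol.** 150 dyads per arm; 300 dyads with a case manager, at most 30 each; 15% dropout; CBI mean 32.5 (SD 18) in control and 24 (SD 12) under treatment; 80% power; alpha 0.05. The sidedness for CBI is not stated and is taken as two-sided; days at home is one-sided.

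**Assumptions.** ICC 0.01 to 0.10 (none is given). Exactly ten managers, the minimum. Each manager carries both active arms equally.

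**Step 1: the plan's own sample size.** For CBI, n per arm = (18² + 12²) × (1.96 + 0.8416)² / 8.5² = 468 × 7.849 / 72.25 = 50.8, so 51, and 51 / 0.85 = 60 with dropout. The planned 150 is more than sufficient, as the protocol says, with power of about 99% at 127 analysed per arm. For days at home no SD is given, so the figure cannot be reproduced. With 127.5 analysed per arm, 80% power at one-sided 0.05 implies a standardised effect of (1.645 + 0.8416) × √(2/127.5) = 0.311.

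**Step 2: cluster size.** 300/30 = 10 managers. Each has 15 dyads per active arm, and 15 × 0.85 = 12.75 are analysed. Analysed per arm: 150 × 0.85 = 127.5.

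**Step 3: variance of active arm against control.** DEFF = 1 + (12.75 − 1) × ICC in the active arm, and 1 in control.
- Equal variances: inflation = (1 + DEFF)/2.
- Protocol SDs for CBI: inflation = (324 + 144 × DEFF)/468. The clustered arm supplies only 144/468 = 31% of the variance, so the inflation is smaller.
- True type I error = 2 × [1 − Φ(1.96/√inflation)].

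| ICC | DEFF | Inflation, equal variances | Type I error | Inflation, CBI SDs | Type I error |
|---|---|---|---|---|---|
| 0.01 | 1.118 | 1.059 | 5.7% | 1.036 | 5.4% |
| 0.02 | 1.235 | 1.118 | 6.4% | 1.072 | 5.8% |
| 0.05 | 1.588 | 1.294 | 8.5% | 1.181 | 7.1% |
| 0.10 | 2.175 | 1.588 | 12.0% | 1.362 | 9.3% |

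The CBI standard error is √(468/127.5) = 1.92 under independence and 1.95 to 2.24 over this range.

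**Step 4: simulation.** Two-sample t-tests with equal variances, ten shared managers, 13 dyads per manager per arm and 4,000 runs per setting gave about 9% against control at ICC 0.05, in line with the formula. UP against UP-TECH gave about 4.5%: a manager effect common to both arms cancels from that contrast.

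**Step 5: power with the correct standard error.** CBI power stays at about 97% to 99%. Days at home has no slack: its stated 80% becomes Φ(0.311/√((1 + DEFF)/127.5) − 1.645), which is 78%, 76%, 71% and 63% at the four ICC values.

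**The case against.** **The analysis plan may deal with this.** The article is condensed, its covariates are examples, and a separate plan could add a manager term. But the article itself names the primary model for both outcomes and a sample size, and neither allows for a structure that the same text creates. Following it as written gives the wrong standard error whenever the ICC is positive.

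**The size is assumed.** This stands. No ICC is given for either outcome. A common 8-day course and monthly meetings with one supervisor would tend to reduce differences between managers. At ICC 0.01 the effect is minor. Ten is also the smallest possible number of managers; more would mean smaller clusters and less inflation.

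**Control is not free of clustering.** This stands in part. Control dyads share districts and visiting nurses with treated dyads, and some of a manager's apparent effect may be the district's service network. Correlation common to all arms largely cancels in a balanced comparison. Only the part specific to the manager matters here.

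**A stronger reading.** A reader might infer that separate managers serve UP and UP-TECH. With 30 dyads in a single arm each (25.5 analysed), type I error would be 6.4% to 18.9% against control. For UP against UP-TECH it would be 7.9% to 29%, with the technology contrast confounded with about five managers per arm. The text does not indicate this. It describes one pool of managers for 300 dyads, all trained in the use of technology, and no separate UP-TECH role. That the assignment is not spelled out is missing detail, not an error.

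**Conclusion.** The concern holds conditionally. The protocol creates clustering by case manager in the two active arms only, then fixes an analysis and a sample size that ignore it. Any positive manager-specific ICC makes standard errors against control too small.

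Under the assumptions in the working, a nominal 5% test is really about 5.7% to 12.0% with equal variances, or 5.4% to 9.3% for CBI with the protocol's SDs. The error would be smaller with more managers or if part of the correlation is by district. It would be larger only if managers were split by arm.

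Two further inferences are not supported. The CBI comparison is not left underpowered; the harm there is false precision. The UP against UP-TECH contrast is not inflated if managers are shared. The point merits a change to the analysis but does not undermine the design.

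**What to change.** Record the case-manager ID for every dyad in UP and UP-TECH. For both primary outcomes, keep the planned ANCOVA covariates and add:
- district as a fixed effect, so that correlation common to all arms is not attributed to managers;
- a random case-manager effect in the active arms only, with each control dyad as its own cluster;
- arm-specific residual variances;
- Satterthwaite or Kenward-Roger degrees of freedom.

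In the Cox model, use a manager-level frailty or a cluster-robust variance.

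The cost is one recorded field and revised analysis wording, with no extra visits or measurements. Intervals against control become somewhat wider. The manager variance will be estimated imprecisely from about ten clusters, which is why the small-sample degrees of freedom are needed.
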